### Trial randomization and blinding

Once a patient signs the informed consent and after the first study visit, he/she will be randomized into one of both treatment arms by one of the investigators using an interactive web response system (IWRS). Patients will be randomized in a 1:1 ratio, using permuted block randomization with blocks of variable sizes (2–4-6) into one of the two intervention parallel groups.

The statistician will be blinded to group allocation. Outcome assessors will be blinded to the maximal extent possible. Participants will of course be aware of the intervention received. Regarding this, participants will be asked not to communicate with the assessors about the intervention received. The therapists providing the experimental intervention will not be involved in the usual care treatment, and vice versa.

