Participants will be recruited through referral from health care workers, spreading of leaflets throughout the campus and online and through members of the advisory boards. All interested individuals can contact the research team for further information. After this initial contact, a formal clinical screening check will be performed. During this, the medical practitioner will perform a standard anamnesis about their COVID-infection and persisting symptoms, medical history, use of medication and perform a standard clinical examination. He will check the eligibility of the possible participant conform the in- and exclusion criteria and if necessary, refer to a specialist for advice and/or further investigation (e.g., in the presence of cardiac without available evaluation). Also, patients who fail to meet the Get Active Questionnaire (GAQ) [19] will not be considered eligible. If the patient is eligible, the medical doctor will obtain informed consent.

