### Primary feasibility outcomes

The first aim of this pilot study is to test trial procedures and processes. This implies running through the full procedures, with the patients, to detect possible challenges. Our main focus in terms of feasibility are patient study burden and recruitment and attrition rates. The patients will be asked during the last visit if the study procedures are acceptable, which will help to make adaptation of the protocol. Next, we should be able to observe recruitment rates and intervene, try to persuade and discuss reasons with the patients to avoid low responses. In that respect, recruitment fewer than anticipated (10/month) and an attrition of 20% will automatically trigger a discussion with the steering committee on how to counter these inappropriate rates. A second aim is to get a better understanding of the data, which is necessary because of the lack of data in this population.

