### Task 1: individualized nutritional therapy

A nutritional interview (45 min) will be performed at baseline. During this interview, a nutritional anamnesis is performed based on standard dietetic practice to assess the usual intake and usual eating patterns. Additionally, the BMI and weight evolution since the COVID-19 infection and/or in the last 3–6 months are assessed. If during this anamnesis, any exclusion criteria are discovered or presumed (e.g., severe gastro-intestinal conditions that lead to rapid weight loss or absorption issues), the participation will be ended or postponed until the medical team can decide if it is safe for the participant. All participants will complete a food diary (last 3 days), that will be analyzed by registered dietitians using the Belgian Food Composition Database Nubel PRO. The control group will be given general nutritional advice in the form of a leaflet with information about healthy nutrition. The intervention group will be followed-up by one of the study dieticians during a weekly tele-consultation in the first 12 weeks (between T0 and T2), aiming at better guidance of participants throughout the intervention period. This is a low-threshold intervention with proven benefit and feasibility, validated in our former trial [18].

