### Sample size

For this pilot we aim for 52 participants. This is in line with Whitehead et al. who recommends a sample size of 25 per treatment arm of interest in a pilot study, accounting for a standardized mean difference of 0.2 in the future definitive RCT with a power of 90%, and two-sided 5% significance [47]. Considering an attrition rate of 20%, 66 patients will be randomized.

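### Study burden is asked about only at the last visit, so everyone who leaves earlier is missing from a primary feasibility outcome

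*Protocol article*

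**What the plan says.** Under Primary feasibility outcomes the protocol article states: "Our main focus in terms of feasibility are patient study burden and recruitment and attrition rates". The same section says how acceptability is obtained: patients are asked about it during the last visit. It describes no other occasion. It also sets two triggers for a steering-committee discussion, recruitment below 10 per month and attrition of 20%, without giving a denominator for attrition.

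The order of entry is consent, first study visit, randomisation. Eligibility criteria and recruitment strategy: "If the patient is eligible, the medical doctor will obtain informed consent". The section Trial randomization and blinding gives the next steps: "Once a patient signs the informed consent and after the first study visit, he/she will be randomized into one of both treatment arms".

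The same parameters are measured at baseline, week 6, week 12 and six weeks later (Assessment battery of the main trial). Baseline also includes intake history (Explanatory measures) and an interview (Task 1): "A nutritional interview (45 min) will be performed at baseline". Task 1 adds that participation may be stopped or put on hold if an exclusion criterion comes to light during that interview.

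Sample size: "For this pilot we aim for 52 participants", and then "Considering an attrition rate of 20%, 66 patients will be randomized".

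**The concern.** Burden is best judged by those for whom it was too much, and these are the people most likely to have left before the last visit. A question put only to those who reach that visit describes acceptability among patients who stayed. This is survivor bias in one of the three outcomes on which the pilot's feasibility verdict rests.

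The population makes such losses plausible. Eligible patients have exercise intolerance, fatigue or muscle pain, and the exercise programme itself plans for symptoms that worsen 12 hours or more after exertion. Some may leave after a first visit with physical tests, questionnaires and an interview, before they are randomised. Others may leave during the 12 weeks or before the final follow-up. Neither group would be asked.

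At stake is the use of the pilot. The acceptability answers are meant to guide changes to the protocol for the definitive trial. If those who found the procedures too heavy are silent, the battery may be carried forward unchanged.

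**Working it through.** **Inputs.** From Sample size: 52 participants wanted, 20% attrition, 66 randomised. From Trial randomization and blinding: "Patients will be randomized in a 1:1 ratio", so 26 per arm. Loss between consent and randomisation (L) is not given; 0% to 20% is assumed for illustration.

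**Reproducing the 66.** Per arm: 26 / (1 − 0.20) = 32.5, rounded up to 33; 2 × 33 = 66. Without rounding by arm: 52 / 0.80 = 65. The stated figure is reproduced and contains no error.

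**Not asked, after randomisation.** 66 − 52 = 14, and 14 / 66 = 21.2%. (20% of 66 is 13.2; the small difference is rounding.)

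**Not asked, counted from consent.** Consents needed C = 66 / (1 − L), rounded up. Not asked = C − 52.

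| Assumed L | C | Lost before randomisation | Not asked in total | Share of consenters not asked |
|---|---|---|---|---|
| 0% | 66 | 0 | 14 | 14/66 = 21.2% |
| 5% | 69.5 → 70 | 4 | 18 | 18/70 = 25.7% |
| 10% | 73.3 → 74 | 8 | 22 | 22/74 = 29.7% |
| 20% | 82.5 → 83 | 17 | 31 | 31/83 = 37.3% |

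At each of these values of L except 20%, those lost after randomisation (14) outnumber those lost before it. A remedy limited to patients who stop before randomisation would therefore miss the group that the plan itself expects.

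**Possible effect on the result.** Let m be the share not asked, a the proportion finding the procedures acceptable among those asked, and b the proportion among those not asked. The reported figure is a; the figure for everyone is (1 − m)a + mb. The difference is a − [(1 − m)a + mb] = m(a − b). It is zero if leavers and completers judge alike. It cannot exceed m, reached when a = 1 and b = 0: 21.2 percentage points among the randomised, and up to 37.3 points from consent at L = 20%. The document has no data on a or b, so only this bound can be given.

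**The case against.** A reader might infer more: that randomising after the baseline visit is itself the flaw, and that patients lost in between are excluded from attrition as the protocol is written. The document does not support this. Taking baseline before allocation is sound, because that assessment cannot then be influenced by knowledge of the arm. Sample size sets a base only for the inflation from 52 to 66; Primary feasibility outcomes gives the attrition outcome no base at all, so exclusion is inferred and not stated. If recruitment is counted at randomisation, losses at baseline would lower the monthly rate and could set off that trigger. Nor does the text say that baseline is the heaviest visit: it has added content, but no durations are given, and equating the first study visit with T0 is a reading, though the natural one.

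Against the narrower point it can be said that the article condenses a fuller protocol, that it plans to discuss reasons with patients when responses are low, and that its largely qualitative approach leaves room to notice early problems. It can also be said that some early losses are not burden at all, since ineligibility may emerge at the baseline interview. The last of these stands and is the reason to report the two kinds of loss separately. The others do not remove the point. The article does state when acceptability is asked, and that moment excludes leavers. Discussing reasons in order to keep up responses is not the same as recording acceptability from those who go. One might read the last visit as the last one each patient happens to attend, but that is often known only afterwards, and no exit contact is described.

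**Conclusion.** The point holds for the burden outcome. The stated rule obtains acceptability only from patients who reach the last visit, and at the planned attrition about 14 of 66 randomised patients (21.2%) would never be asked, plus everyone lost between consent and randomisation. The cause is the timing of the question, not the timing of randomisation, and moving randomisation would not cure it.

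That the result will look too favourable is likely but not certain: it assumes that leavers find the procedures less acceptable than completers do. The 25.7% to 37.3% range rests on an assumed pre-randomisation loss of 5% to 20%; the true loss is unknown and may be small. The missing denominator for the attrition trigger is a supporting clarification and no more. The sample size is unaffected.

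**What to change.** In Primary feasibility outcomes, state that every consented patient who stops, before or after randomisation, will be asked the same acceptability question and the reason for leaving at the time of withdrawal. Report these answers beside those from the last visit, with the number asked and the number who answered in each group.

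As a clarification in the same section, state that the 20% attrition trigger is counted among randomised patients. Report loss between consent and randomisation as a separate figure out of those who consented, split into found ineligible and withdrawn, so that ineligibility is not read as intolerance.

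Keep randomisation after the first study visit and keep 66 randomised.

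The cost is a few lines of protocol text and a brief contact at withdrawal, for about 14 randomised patients at the planned rate and for those lost earlier (4 to 17 under the assumed range). Some leavers will not reply, so the bias is reduced and not fully removed. The feasibility result may look less favourable.

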### Sample size

For this pilot we aim for 52 participants. This is in line with Whitehead et al. who recommends a sample size of 25 per treatment arm of interest in a pilot study, accounting for a standardized mean difference of 0.2 in the future definitive RCT with a power of 90%, and two-sided 5% significance [47]. Considering an attrition rate of 20%, 66 patients will be randomized.

### Statistical analysis

The focus is primarily qualitative and unstructured but there is a minor but important statistical focus which is descriptive, which focuses on the full distribution of observations in general and the dispersion in particular. All parameters will be analyzed descriptively by treatment arm, there will be no formal hypothesis testing and a repeated measures model will be used to derive an estimate of the treatment effect. While the actual analysis can be performed as planned, because all data required for that should be available, any statistical test would presumably be underpowered.

### Data handling and monitoring

To define data management practices the data manager developed a clinical data management plan (CDMP), that was reviewed by the principal investigator and the trial monitor. Besides the CDMP, multiple standard-operating procedures were developed for screening, randomization, assessments during study visits, and individual nutritional therapy. In case of protocol deviations, these will be reported in the Trial Master File and the ethics committee will be notified.

## Discussion

There is need for a multidisciplinary approach when dealing with long COVID (post-COVID syndrome) manifestations. The UNLOCK study will investigate whether a personalized multimodal treatment (tailored physiotherapy and individual nutritional therapy) is able to improve functional performance recovery faster than standard physiotherapy alone. The choice for functional endpoints is motivated by the fact that patients suffering long COVID experience difficulties performing their daily activities whether because of exertional intolerance (fatigue, dyspnea, widespread pain, deconditioned state…) or cognitive difficulties (attention and memory deficits, brain fog…).

The rationale for the combination of both interventions (physical therapy and nutritional optimization) is based on our clinical expertise and the feedback from our long COVID patients regarding the need for a multidisciplinary approach to account for their complaints (including feelings of fatigue, post-exercise symptom exacerbation, and loss of smell and taste). In addition, the rationale for not including a separate study arm (only personalized physical exercise program), which would allow us to investigate the contribution of the nutrition component, is based on feasibility issues as well as to respond to the cry-out and sense of urgency, reported by the long COVID patient community.

Because of the lack of clear data on long COVID patients and the fact that this group is very heterogenic, we aim with the present protocol to prepare a randomized controlled study that addresses the effectiveness of a personalized multimodal treatment. This pilot will offer us necessary information on the feasibility of the future experiment.

## Data Availability

Not applicable in this section.

## Abbreviations

1-MSTS: 1-Minute sit-to-stand test
6-MWT: 6-Minute walk test
AEs: Adverse events
CDMP: Clinical data management plan
eCRF: Electronic case report form
En%: Energy requirements
ESPEN: European Society of Clinical Nutrition and Metabolism
EQ-5D-5L: 5-Level EuroQol 5 dimensions
HADS: Hospital Anxiety and Depression Scale
GAQ: Get Active Questionnaire
IPQ: Illness perceptions questionnaire
IWRS: Interactive web response system
MFI-20: Multi-dimensional Fatigue Inventory
mMRC: Modified Medical Research Council
PCFS: Post-COVID-19 Functional Status
PESE: Post-exertional symptom exacerbation
PMR: Physical Medicine and Rehabilitation
PMT: Personalized multimodal treatment
RCT: Randomized controlled trial
SAEs: Severe adverse events
WPAI: Work Productivity and Activity Impairment
